#### Interim analysis

Interim analysis will be monitored by an independent Data Safety Monitoring Committee. We plan an interim analysis for futility and safety after 100 participants in the ASB *treat* study. This analysis will be done by an independent person who will be unaware of the allocation of treatment when data are judged for effectiveness.

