#### ASB treatment trial

Women eligible for the ASB *treatment trial* will be identified by the laboratory personnel participating in this study. A research midwife or -nurse will contact these women for participation in the treatment trial.

Before entering the study, women will be informed about the aims, methods, reasonably anticipated benefits and potential hazards of the study. Participation is voluntary and withdrawal of consent to participate is possible at any time during the study. After giving sufficient information, written informed consent will be asked for. Women eligible for the ASB *treatment trial* who do not give informed consent, will be registered. Nitrofurantoin will not be offered to these women.

After participant data have been entered in a web based database, computerized randomisation will take place. The women with ASB will be randomised 1:1 for nitrofurantoin and placebo. Women without ASB (used for blinding of bacteriuria status) will always receive placebo.

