### Intervention

Each study participant will be given a jar labelled “ASB *treat* study” which contain either 100 mg capsules of nitrofurantoin (Nitrofurantoin MC, TioFarma, the Netherlands) or identical-appearing capsules of placebo (TioFarma, the Netherlands).

The oral study medication will be self-administered twice a day for 5 consecutive days. The label codes indicating nitrofurantoin or placebo are blinded for the participants and researchers. The deblinding list is present in the central pharmacy. For emergency cases, a closed envelope with the label codes is also available at the study centre. The data will be disclosed to the researchers in case of emergencies and otherwise after collection and analysis of the primary outcomes. Researchers involved in the follow up program of the offspring of women participating in this study will remain blinded for a longer period. For purpose of the interim analysis the label codes will become available to the epidemiologist involved in the study as A and B.

All participants who receive study medication -i.e. the screen positives as well as the random subsample of screen negatives-, will have follow up dipslides done 1 week after the end of treatment. Participants with a persistent positive culture and a subsample of participants with a negative culture will receive again (blinded) study medication. The participants who received nitrofurantoin will again receive nitrofurantoin, placebo participants will again receive placebo. One week after this second intervention, once again a dipslide is performed.

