### Statistical issues

#### Sample size calculation

Among women positive for ASB, we anticipate the occurrence of the primary outcome (delivery before 34 weeks and/or pyelonephritis) to be 10% in the treatment group and 25% in the no treatment group. If ASB is not treated, 20% of pregnancies with ASB will be complicated by pyelonephritis compared to 2% of pregnancies without ASB [24]. Treatment of ASB results in a decrease of pyelonephritis compared to women who were not treated. Using a two-sided test with an alpha 0.05 and a beta of 0.8, 220 women with ASB (110 per arm) are needed in the study. Anticipating a 5% incidence of ASB, we need to screen 4.400 women. Obviously, final recruitment statistics will depend on the screen positive rate, which is one of the study questions. From our previous experience in the Triple P trial [25] we learned that Dutch women are very reserved in taking study medication for asymptomatic conditions in pregnancy. If during this trial it becomes clear that very few women consent to participate in the ASB treat study we will not increase our screening cohort indefinitely to reach our planned randomisations.

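### The interim futility judgement is made without knowing which arm is nitrofurantoin, so a trend of harm cannot be told from a trend of benefit of the same size

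*Protocol article*

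**What the plan says.** The Interim analysis section gives the look its timing and its two purposes: "We plan an interim analysis for futility and safety after 100 participants in the ASB" treatment study. It places the look under an independent Data Safety Monitoring Committee (DSMC) and then sets the masking: "This analysis will be done by an independent person who will be unaware of the allocation of treatment when data are judged for effectiveness".

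The Intervention section describes how the codes are handled: "For purpose of the interim analysis the label codes will become available to the epidemiologist involved in the study as A and B". It also says where the key is kept: "The deblinding list is present in the central pharmacy". A sealed envelope at the study centre is for emergencies. Otherwise the researchers learn the allocation only once the primary outcomes have been collected and analysed.

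The section on the DSMC lets it order a further interim analysis and end the trial early. No section says that the DSMC, or the person doing the interim analysis, is told which code is nitrofurantoin when the interim is judged.

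**The concern.** The Outline section states the trial's objective as finding out whether nitrofurantoin lowers the risk of preterm delivery and/or pyelonephritis. Futility therefore means that nitrofurantoin is unlikely to show that reduction. A reader who has only A and B can use the size of the difference but not its sign. If one arm has clearly more events, this is promise when that arm is placebo and the opposite when that arm is nitrofurantoin. A masked reader would call both results not futile.

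The problem does not depend on the masking failing. It arises when the masking works as written. At stake is the first stated purpose of the look: a drug trending the wrong way passes the futility judgement, and an inert drug passes it more often than it would if the arms were identified.

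**Working it through.** **Inputs from the article.** Event rates: "to be 10% in the treatment group and 25% in the no treatment group". Size and error rates: "Using a two-sided test with an alpha 0.05 and a beta of 0.8, 220 women with ASB (110 per arm) are needed in the study" (I read the 0.8 as power). Allocation: "The women with ASB will be randomised 1:1 for nitrofurantoin and placebo". Interim after 100 women, taken as 50 per arm, so the information fraction is t = 50/110 = 0.4545.

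**The plan's own figure.** Two proportions, 10% vs 25%, two-sided 0.05, power 80%:
- Uncorrected: n = [1.96·√(2·0.175·0.825) + 0.842·√(0.10·0.90 + 0.25·0.75)]² / 0.15² = 99.5, so 100 per arm (200 in total).
- With continuity correction: 112.5, so 113 per arm (226 in total), within 3% of the stated 220.
- Power at 110 per arm is 83.8%.

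The stated size is sound enough to serve as the base for what follows.

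**One data set, two meanings.** Suppose the interim shows 5/50 and 12/50 events.
- Pooled rate 0.17; standard error √(0.17·0.83·2/50) = 0.0751; |z| = 0.14/0.0751 = 1.86.
- Current-trend conditional power: CP = Φ[(z/√t − 1.96)/√(1 − t)], with √t = 0.674 and √(1 − t) = 0.739.
- If the 5 events are on nitrofurantoin: Φ[(2.764 − 1.96)/0.739] = Φ(1.09) = 86%.
- If the 12 events are on nitrofurantoin: Φ[(−2.764 − 1.96)/0.739] = Φ(−6.40), effectively zero. Even if the design effect is assumed for the remaining women it is 1.4%.
- Labelled A and B, the two tables are identical, so no rule applied to them can separate the cases.

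**Size under an assumed rule.** The article gives no futility threshold. Assume stopping when current-trend CP is below 20%. Solving for z: √t·(1.96 − 0.842·0.739) = 0.902. With the arms identified, stop if z (positive when nitrofurantoin is better) is below 0.902. On A/B labels, stop if |z| is below 0.902. Exact binomial enumeration at 50 per arm gives these stop probabilities:

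| Nitrofurantoin / placebo | Arms identified | A/B only |
|---|---|---|
| 35% / 25% (harm) | 98% | 41% |
| 25% / 25% (no effect) | 81% | 62% |
| 25% / 10% (full reversal, extreme) | 99.8% | 13% |
| 10% / 25% (planned benefit) | 13% | 13% |

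**Sensitivity to the cut-off (10% to 30%).**
- Harm 35% / 25%: 96–98% with arms identified, 32–45% on A/B labels.
- No effect at 25%: 75–85% against 49–70%.
- Full reversal: at least 99.7% against 8–17%.

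**A different kind of conditional power.** If CP is computed under the design effect, the drift is 0.15/√(2·0.175·0.825/110) = 2.93. Even z = 0 then gives Φ[(2.93·0.5455 − 1.96)/0.739] = Φ(−0.49) = 31%. With the sign removed, CP can never fall below 31%, so at cut-offs up to 30% the A/B look never stops. With the arms identified it stops under no effect (25%) in 20–45% of looks over the same cut-offs.

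**The case against.** Several points on the other side carry weight.

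- **The masking is worded for effectiveness only.** The look also covers safety, and the clause does not mask that reading. No section masks the DSMC, which receives serious adverse events and can end the trial. A reader might infer that a harmful drug would go unnoticed and that women would go on being exposed. The documents do not support that. The DSMC could ask the pharmacy for the key. What remains is that no section provides for this, and an A/B gap that looks promising gives no stated reason to ask.
- **The article is condensed.** The threshold and the routine of the DSMC may well be in a charter or the full protocol, and their absence is not criticised here. The masking of the effectiveness judgement, however, is a rule the article states.
- **The A/B sentence may be over-read.** It names the epidemiologist involved in the study, while the Interim analysis section names an independent person. The article does not say that they are the same. Even so, the masking clause alone produces the problem.
- **The numbers rest on an invented, mechanical rule.** This is true. The full reversal is an extreme case and also puts placebo at 10% rather than the planned 25%. The 35% vs 25% row keeps placebo at the planned rate and is the fairer illustration. An inert drug is still stopped in most looks at the 20% cut-off.
- **A symmetric futility reading is possible.** The final test is two-sided, and one could define futility as unlikely to show any difference, leaving harm to the safety reading. This is coherent, but it does not answer the stated objective of reducing risk, and the article does not say that it is meant.

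**Conclusion.** The point holds for the futility judgement. As written, that judgement cannot tell benefit from harm of equal size. Under the assumed 20% rule the look stops a harmful drug (35% vs 25%) in 41% of trials instead of 98%, and an inert one (25%) in 62% instead of 81%. Under the planned benefit, identifying the arms leaves the stop rate at 13%. The sizes depend on the assumed rule, on 50 women per arm and on complete outcome data at the look; the direction is the same for every cut-off tried.

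It does not follow that harm must be missed, since the safety reading and the DSMC lie outside the masking clause. For that reason this is something that should be fixed, not a defect that invalidates the trial.

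**What to change.** In the Interim analysis section, replace the masking sentence. The independent statistician, and the DSMC in closed session, receive the arm identity when the interim is judged. Futility is judged on the signed nitrofurantoin-minus-placebo effect. Align the A/B sentence in the Intervention section with this. Participants, investigators and the study team stay masked, including the epidemiologist involved in the study if that is not the independent person.

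Do not add a rule that every trend against nitrofurantoin counts as a safety signal. With no effect at 25%, nitrofurantoin has more events than placebo in about 45% of looks (exact enumeration, 50 per arm). The DSMC should see the signed result and judge it.

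The cost is a sentence or two in the protocol or DSMC charter. The downside is small: one independent person and the DSMC know the key.

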### Statistical issues

#### Sample size calculation

Among women positive for ASB, we anticipate the occurrence of the primary outcome (delivery before 34 weeks and/or pyelonephritis) to be 10% in the treatment group and 25% in the no treatment group. If ASB is not treated, 20% of pregnancies with ASB will be complicated by pyelonephritis compared to 2% of pregnancies without ASB [24]. Treatment of ASB results in a decrease of pyelonephritis compared to women who were not treated. Using a two-sided test with an alpha 0.05 and a beta of 0.8, 220 women with ASB (110 per arm) are needed in the study. Anticipating a 5% incidence of ASB, we need to screen 4.400 women. Obviously, final recruitment statistics will depend on the screen positive rate, which is one of the study questions. From our previous experience in the Triple P trial [25] we learned that Dutch women are very reserved in taking study medication for asymptomatic conditions in pregnancy. If during this trial it becomes clear that very few women consent to participate in the ASB treat study we will not increase our screening cohort indefinitely to reach our planned randomisations.

### Economic evaluation

#### General considerations

The economic analysis will be performed from a societal perspective. Both costs and outcomes will be discounted with a discount rate of 5%. The economic analysis of the trial itself is not of interest. If nitrofurantoin is found to decrease the probability of pyelonephritis or preterm delivery, then the savings due to decreased maternal and neonatal admission will always outweigh the costs of nitrofurantoin, which are negligible. The true economic question to be answered, when the treatment trial shows a beneficial effect, is whether the costs of screening (number needed to screen to detect one woman with ASB) outweigh the cost reduction and health benefits from treatment with nitrofurantoin.

#### Cost analysis

The study design will enable us to compare the costs and effects of the following strategies:

I. no screening for ASB

II. screening for ASB and treatment of women with ASB

For each of these strategies, we will calculate the costs as well as the effects in terms of pyelonephritis or preterm delivery. In the cost-effectiveness analysis, we will then calculate the costs per prevented case of pyelonephritis or preterm delivery. Thus, the cost-effectiveness analysis will assess the balance between number needed to treat and number needed to screen.

### Data safety monitoring committee

Serious Adverse Events (SAEs) and Suspected Unexpected Serious Adverse Reactions (SUSARs) will be reported to a Data Safety Monitoring Committee (DSMC). The DSMC can order to perform an extra interim analysis and, if indicated, terminate the trial prematurely.

### Ethical considerations

This study is approved by the National Central Committee on Research involving Human Subjects (CCMO - NL35375.018.11) and by the ethics committee of the Academic medical centre Amsterdam (ref. no MEC 2011_073).

## Discussion

To our knowledge there are no other ongoing trials in the Netherlands or other countries, evaluating a screen and treat strategy for ASB with the dipslide technique (http://www.controlled-trials.com/mrCT/). This trial will provide evidence for the usefulness and cost-effectiveness of screening for ASB at 16–22 weeks of pregnancy with a dipslide and subsequent nitrofurantoin treatment among low risk women.

## Abbreviation

ASB, Asymptomatic bacteriuria; CFU, Colony forming units; ml, Millilitre; UTI, Urinary tract infection; SAE’s, Serious adverse Events; SUSARS, Supspected Unexpected Serious Adverse Reactions; DSMC, Data Safety Monitoring Committee.
